### Assessment and timeline of the study

2.4

The study is comprehensive of clinical, instrumental, and biological assessments that will be performed by blind raters, in the “on” medication status of patients, at the same time of day for each subject. Assessment timing is reported in Figure 1. Clinical, neuropsychological, and instrumental variables such as postural sway and gait analysis will be collected at baseline (T0), at the end of the treatment (T1), and 3 months after the end of treatment (T2). At 6 months after the end of treatment (T3) a phone interview will be performed to verify the occurrence of falls in a relevant time frame. The same assessment protocol will be performed at each time point (T0, T1, T2) with some exceptions: automatic acquisition of gait parameters using C-Mill in C-Gait mode will be collected only at T1 and T2 in a subgroup of cases; at T1, a 5-point Likert scale will also be administered to register patient satisfaction; during the phone interview at T3 only the falls questionnaire will be administered; biological samples will be collected at T0 and T1.

**Figure 1 fig1:**
[figure not shown]
Timing of clinical, instrumental, and biological assessments that will be performed in the VIRTREAD-PD study. Clinical, neuropsychological, and instrumental variables will be collected at baseline (T0), at the end of the treatment (T1), and 3 months after the end of treatment (T2). At 6 months after the end of treatment (T3) a phone interview will be performed. Image created with BioRender.com.

#### Clinical assessment

2.4.1

Clinical assessment will be performed by raters experienced in PD patients’ evaluation. The Montreal Cognitive Assessment (MoCA) (40) and Beck Depression Inventory II, Italian version (BDI) (41) will be used to exclude patients with dementia and severe depression. All enrolled participants will be assessed by the following scales/tests:

the Performance Oriented Mobility Assessment (POMA) (36) to evaluate gait (POMA-G) and balance (POMA-B)the MDS-UPDRS part III (42, 43) to evaluate different symptoms and signs in PDthe Italian version of the Parkinson’s disease cognitive rating scale (PD-CRS) (44) to evaluate global cognitive functionsthe Trail-Making-Test A and B (TMT-A and B) (45), the Stroop Test (46), and the Symbol Digit Test (SDT) Italian oral version (47) to evaluate attention and executive functionsthe Parkinson’s Disease Questionnaire (PDQ-39-IT) (48) to evaluate the perceived health-related quality of lifethe Modified Parkinson Activity Scale (MPAS) (49) and the TUG test (50) to evaluate functional mobilitythe 6-Minute Walking Test (6MWT) (51) to evaluate walking endurance; the test will be performed indoors along a 30 m corridor, following the American Thoracic Society guidelines (52)the Freezing Of Gait Questionnaire (FOG-Q) (53) to evaluate the frequency and duration of freezing episodesthe Falls Efficacy Scale, Italian version (FES-I) (54) to evaluate the fear of falls in different situations of riskthe fall questionnaire (55) to account for the number of fallsthe Numerical Rating Scale (NRS 0–10) (56) to evaluate current painthe modified Barthel Index (mBI) (57) to evaluate functional independence in the basic activities of daily living

At T1, participants will be also asked to rate their satisfaction with the treatment using a 5 Point Likert Scale (range: 1–5, where 5 indicates a very high appreciation).

To avoid inter-rater variability, participants will be evaluated by the same rater (1–2: Neurologist or Physiatrist; 3–5: Neuropsychologist; 6–12: Physiotherapist) at different time points. All scales will be repeated in the same version, except for MoCA, for whom parallel Italian versions are available (58).

#### Instrumental assessment

2.4.2

Instrument-assisted testing will be aimed at assessing postural sway and overground and treadmill gait. Blinded Physiotherapists will carry out an assessment through a force platform (AMTI OPT464508HF sampling at 1,000 Hz; AMTI, USA), the C-Mill, the Optogait and Witty systems (by Microgate, Italy).^1^

##### Postural sway

2.4.2.1

The postural sway will be assessed by asking the patient to maintain standing statics with feet together while standing as still as possible in 6 different conditions (feet apart, feet together, feet in tandem position, both with eyes open and eyes closed) lasting 40 s. The assessment will be performed on the force platform and then again on C-Mill.

##### Overground gait

2.4.2.2

The overground gait parameters will be evaluated using the Optogait system (Optogait, Microgate S.r.l., Bolzano, Italy) and two pairs of photocells (WITTY, Microgate Srl; Bolzano, Italy; 0.001-s accuracy), as reported in Figure 2. Optogait is an optical sensing system for kinematic gait analysis, consisting of a transmitter bar and a receiver bar. Between the two bars, there is a continuous light beam that is interrupted when the patient’s feet are interposed during gait. The system detects the dimensions of the patient’s foot and estimates the spatial/temporal gait parameters. Witty is a system composed of pairs of photocells that record elapsed split times when the subject crosses the line between the photocells. For the present study, we will use a 10-meter Optogait corridor with two pairs of photocells placed to demarcate the central 4 m of the corridor. Participants will be asked to walk through the corridor at self-selected walking speed (SSWS) and at high speed (HS, defined as the maximal speed that can be safely maintained for a short distance) (51). Three trials at each speed will be performed, with a brief rest between trials, and the mean values will be used for the statistical analysis. All variables will be measured from data recorded in the central 4 m of the corridor, to exclude the acceleration and deceleration periods at the start and end of walking phases, respectively, and thus measure representative steady-state walking data. The following gait parameters will be collected: mean speed, step and stride lengths, cadence and duration of stance, swing, and double-support phases.

**Figure 2 fig2:**
[figure not shown]
Schematic representation of the setting planned for the overground gait assessment that includes the optical sensing system Optogait and a 10-m Optogait corridor with two pairs of photocells placed to demarcate the central 4 m of the corridor. Image created with BioRender.com.

##### Treadmill gait

2.4.2.3

At T1 and T2, all participants will perform the C-Gait test, a preset test of the C-Mill that includes 6 applications of AVR (stepping stones, obstacle mode, walking area, tandem, slalom, and tracks) interspersed with free walking phases. Some applications will be among those exercised by the experimental group during the training and others will be new to participants in this group as well. The C-Gait report provides indications regarding the kinematics during different AVR applications and the success rate of the test.

#### Biological procedures

2.4.3

Biological samples will be collected at T0 and T1 using serum separation tubes. Forty-five minutes after the blood draw, samples will be separated using centrifugation at 2,500 × *g* for 10 min. Then serum will be aliquoted in cryogen micro vials and stored at −20°C until transfer in dry ice to the LABION, where the analysis will take place.

Serum samples will be used to quantify NfL using the automated immunoassay platform Ella (ProteinSimple, Bio-Techne, MN, USA). Human NF-L Simple Plex assay will be used following the manufacturers’ instructions. A single well will be used for each sample as triplicates assays are automatically performed in Simple Plex assay microfluidic platform.

For cEV isolation, after thawing, serum will be centrifuged at 10,000 × *g* for 10 min. Then, cEVs will be isolated by size exclusion chromatography (SEC) using commercial columns (qEV single Gen2, 70 nm, Izon Science Limited, Christchurch, New Zealand) and Automatic Fraction Collector (AFC, Izon Science Limited). Following the manufacturer’s instructions, 150 μl of serum will be loaded onto the SEC column and cEVs containing fractions will be retained after elution. cEV suspension will be then concentrated by ultracentrifugation (100,000 × *g* for 70 min; L7-65; Rotor SW60; Beckman Coulter, Brea, CA, USA) at 4°C. cEVs will be characterized in agreement with ISEV guidelines (54) by nanoparticle tracking analysis (NTA; NanoSight NS300, Malvern Panalytical, Malvern, UK) and western blot analysis.

Immunoblotting will be performed to characterize cEVs. Briefly, cEV concentrated suspensions from T0 and T1 samples will be obtained by pooling together specimens from multiple subjects. Lysis of cEVs will be performed by sonication, then proteins re-suspended in SDS sample buffer protease inhibitors will be loaded on the electrophoresis gel under reducing conditions. Proteins will be transferred to nitrocellulose membrane and antigens will be probed with primary antibodies specific for cEV protein markers followed by incubation with secondary antibodies conjugated with HRP.

For the Raman analysis, a previously optimized protocol will be followed (34). In brief, cEVs from T0 and T1 samples will be analyzed by means of a Raman micro-spectroscope (LabRAM Aramis, Horiba Jobin Yvon S.A.S, Lille, France). 5 μL of cEVs concentrated suspension will be lied onto a calcium fluoride slide (Crystran, Poole, UK). Spectra will be acquired on the air-dried drop with a 532 nm laser line in the spectral ranges 600–1,800 cm^−1^ and 2,600–3,200 cm^−1^, with the following acquisition settings: 50× objective, 1,800 grooves/mm diffraction grating, 400 μm entrance slit, confocal mode (600 μm pinhole). Instrument calibration will be performed using Silicon reference peak at 520.7 cm^−1^. Labspec6 and Origin2023b (OriginLab Corporation, Northampton, MA, USA) will be used for Raman spectra acquisition, post-processing, and data analysis.

Biological procedures referred to cEV analysis are shown in Figure 3.

**Figure 3 fig3:**
[figure not shown]
Schematic representation of the sequential events required for the biological procedures: after the recruitment of subjects, blood withdrawal and serum separation will be performed. Serum will be frozen and stored until subsequent cEVs isolation by size exclusion chromatography and ultracentrifugation. cEVs successful isolation will be verified with standard procedure prior to biochemical characterization by Raman spectroscopy using a calcium fluoride substrate and green laser line. Raman spectra will be analyzed and correlated with clinical data. Image created with BioRender.com.

### Interventional protocol

2.5

Intervention in both groups will be performed using the Motek’s C-Mill, with three sessions of treadmill training per week, every day at the same time during the “on” period of the participant, for 8 weeks. Participants will be encouraged to avoid using the side support bars during training, but a brief period (15-min) of familiarization with the task, during which intermittent support on the bars will be allowed, will be conducted during the first three sessions before starting the training. For all subjects, the training will be customized and progressive in gait speed and duration; for the experimental group, the difficulty of AVR applications will also gradually increase. The progression will be based on the participant’s level of performance, but will follow fixed predetermined rules. In detail, gait speed will be set at 80% of the individual’s overground walking speed at the beginning of training, and will be weekly increased by 10% to a maximum of 120% of that speed; at the beginning of training, the training duration will be 25 min, including 5 slots of exercise lasting 5 min, with a 4-min rest between each slot; every 2 weeks it will be increased by 1 min per slot, until a maximal duration of 45 min in the last 2 weeks of treatment. However, the progression will be applied considering the subject’s tolerance, i.e., the ability to keep the heart rate within safety limits and without subjective discomfort, and to walk without having to brace on the side bars.

Participants assigned to the experimental group will exercise five AVR applications (one for each slot of training): “nature island,” “stepping stones,” “walking area,” “obstacles avoidance,” and “tracks.” These applications train balance and changes in walking speed, promote gait adaptation strategies and strategies to overcome freezing of gait, in a safe and controlled environment; moreover, information to promote proper walking is provided, including feedback on gait parameters such as stride length, cadence and symmetry. Five difficulty levels will be prepared for each C-Mill application, with transition between levels set at a success rate of 80%.

In case of discontinuation of treatment (one or more sessions missed), the treatment will be restarted with the gait speed, trial duration, and, for the experimental group, level of difficulty used in the last completed session. During treatment, the participants’ heart rate (HR) will be measured with a chest-band device; in case the heart rate exceeds the safety threshold (75% of HR max, calculated as 220-age for males and 200-age for females), the treadmill speed will be lowered until parameter normalization.

Pharmacological therapy is requested to be stable until the end of the intervention to minimize the effect of external factors on motor, functional, cognitive performances, and biological measures.

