
Concerning treatment, the main innovation in VIRTREAD-PD is the use of the TT+AVR. As in Mirelman (24), we structured an incremental protocol for the time and duration of 5 walking slots in the rehabilitation sessions. In order to administer treatments tailored to the performance of the individuals involved in the study, training progression was planned in line with a predefined progression plan. Due to the intimate association between motor performances and attentive/executive functioning in PD and as suggested by previous research (23), we included the “obstacle avoidance” task among the AVR applications, targeting the “motor-cognitive interactions,” to improve gait performances and reduce fall risk. Duration and frequency of training are planned as reported in the literature as effective on gait and balance (ranging from 4 to 8 weeks, including 12–20 sessions) (11, 17). In conclusion, this study will compare the effects of 2 rehabilitation protocols on motor symptoms in PD. To our knowledge, this is the first randomized controlled study specifically designed to enroll only PD patients where the effect of conventional TT is compared with that of TT with AVR applications. Innovative elements and strength points of the protocol are represented by a multidimensional approach using both clinical and instrumental assessments, the predefinition of an algorithm for treatment customization, and the application of an innovative method to explore potential biomarkers of neuroplasticity and potential prognostic biomarkers. The results of this study will provide new insight to personalize and possibly optimize the effects of technological rehabilitation for PD patients.

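### The session-duration rule does not reproduce its own end point: as written it reaches 40 min in weeks 7–8, not the stated 45 min

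*Protocol article*

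**What the plan says.** All the inputs stand in section 2.5 (Interventional protocol) of the protocol article.

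- Programme length and frequency: "with three sessions of treadmill training per week, every day at the same time during the “on” period of the participant, for 8 weeks".
- Starting duration and structure: "the training duration will be 25 min, including 5 slots of exercise lasting 5 min, with a 4-min rest between each slot".
- Progression and end point: "every 2 weeks it will be increased by 1 min per slot, until a maximal duration of 45 min in the last 2 weeks".

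The section describes the progression as set in advance and applies the duration part to every participant; only the difficulty of the AVR applications is specific to the experimental arm. It also makes progression subject to what the participant tolerates. The experimental arm has five applications, one per slot, which confirms the number of slots.

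A related sentence in section 3 (Discussion) says that the duration and frequency of training follow published programmes, "ranging from 4 to 8 weeks, including 12–20 sessions".

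**The concern.** The start, step, interval, programme length and end point of a fixed progression are tied together: any four determine the fifth. Here all five are printed, and they do not agree. A therapist who applies the step rule misses the stated maximum, and one who delivers the stated maximum breaks the step rule.

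The progression algorithm is part of the intervention in both arms, and the Discussion lists its predefinition among the strengths of the study. The conflict falls in weeks 7–8, directly before T1, when the primary outcome (POMA-G) is measured. What is at stake is whether the dose can be delivered, reported and replicated as written.

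**Working it through.** **Inputs (section 2.5):** 8 weeks; 3 sessions per week; 5 slots; 5 min per slot at the start; +1 min per slot every 2 weeks; 4 min rest between slots; stated duration in the last 2 weeks, 45 min.

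**Step 1: the starting figure.** 5 slots × 5 min = 25 min. This reproduces the stated start and shows that the durations exclude rest.

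**Step 2: the progression.** Session duration in week w = 5 × (5 + floor((w − 1)/2)) min.

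| Weeks | Min per slot | Exercise only | With four 4-min rests (+16) |
|---|---|---|---|
| 1–2 | 5 | 25 | 41 |
| 3–4 | 6 | 30 | 46 |
| 5–6 | 7 | 35 | 51 |
| 7–8 | 8 | **40** | **56** |
| 9–10 (outside the programme) | 9 | 45 | 61 |

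The stated 45 min is not reproduced in weeks 7–8 by either column.

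**Step 3: other readings.**

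- A rest after every slot (five rests, +20 min) gives 45 min in weeks 1–2 and 60 min in weeks 7–8, so 45 falls at the wrong end.
- Number of steps needed: (45 − 25)/5 = 4, but only three fit before the last 2-week block.
- With three steps, 45 min needs a starting slot of (45 − 3 × 5)/5 = 6 min, or a step of (45 − 25)/(3 × 5) = 1.33 min per slot. Neither is stated.
- With the stated start and step, an interval of 1.5 weeks would reach 45 min by week 7, but the stated interval is 2 weeks.

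These variants only show that each repair changes a printed figure. They are not proposals.

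**Step 4: size.** Each 2-week block has 3 × 2 = 6 sessions.

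- By the step rule: 6 × (25 + 30 + 35 + 40) = 780 min.
- With 45 min in the last block: 6 × (25 + 30 + 35 + 45) = 810 min.
- Difference: 30 min in total, 30/780 = 3.8%. Per session in the last block: 5/40 = 12.5%.

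**Side check: number of sessions.** 3 × 8 = 24 planned sessions, against the 12–20 that the Discussion gives for the literature it follows. The 8 weeks do lie within the cited 4–8.

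**The case against.** The best defence of the text is that delivered duration is individual anyway. Progression depends on tolerance, and after a missed session training resumes at the last completed level. Both provisions can only hold or slow the increase, so neither turns 40 min into 45. Section 2.3 allows missed sessions to be made up at the end, but this replaces lost sessions and adds no increment. Nor can 45 min be read as a ceiling that need not be reached, because the text places it in the final 2 weeks.

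The objection about size stands. Weeks 1–6 are fully determined, the uncertainty is one step in 6 of 24 sessions, and the randomisation, sample size and analysis are untouched.

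A reader might infer that training volume is confounded with AVR, since therapists know the arm and could resolve the ambiguity differently in each. The documents do not support this. The duration rule is written for all participants, and nothing suggests that the last step would be handled differently by arm.

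A reader might also add the sex-specific constants in the heart-rate limit of section 2.5. No other passage contradicts them, so they are not part of this inconsistency.

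On the session count, the 12–20 describes published programmes and is not this trial's dose. Section 2.3 also permits up to 5 missed sessions, so a participant who stays in the study may complete as few as 24 − 5 = 19. That leaves a loosely worded sentence in the Discussion, not a conflict within the intervention rules.

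**Conclusion.** The inconsistency is certain: the printed rule leads to 40 min per session in weeks 7–8, and the same sentence says 45. The 3.8% in total minutes takes weeks 1–6 as printed and assumes full attendance and full progression. If the misprint lies in another input, such as the starting slot or the programme length, the difference in total would not be this one, and the document gives no sign of which figure is meant. The 40 min is what the rule implies, not necessarily the intended dose.

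The slip applies equally to both arms and does not by itself bias the comparison of TT+AVR with TT. Its consequence is a prescribed dose that cannot be reproduced as written. Severity: minor to moderate. The mismatch between 24 planned sessions and the cited 12–20 is a minor side note.

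**What to change.** Reconcile the starting duration, the increment per slot, the interval between increases, the programme length and the stated maximum so that one schedule reproduces all of them, and state whether rest is counted in session duration. A short table of minutes per slot and per session by 2-week block would settle it. Which figure changes is for the investigators to decide; this review takes no position on the dose.

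In the Discussion, reconcile the sentence on the literature basis with the 24 planned sessions.

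The cost is a short text correction and a note to the treating physiotherapists. No design or analysis element changes.

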### Outcome measures

2.6

The primary outcome is the difference in gait performance assessed by the POMA-G scale between the TT+AVR and the TT group at T1. The secondary outcomes are differences in mobility (measured by POMA-G at T2 and POMA-B at T1 and T2), in kinematic gait parameters assessed at T1 and T2, measured by the Optogait system, differences in other motor and non-motor symptoms at T1and T2, patients’ satisfaction, assessed with a 5-point Likert scale, and adherence to the treatment.

Exploratory outcome measures include changes in NfL concentration and change in individual Raman spectra of blood-derived cEVs before and after treatment. The correlation between Raman spectra of blood cEVs and the rehabilitation outcome will be assessed (the biological characterization of patients at T0 analyzing cEVs performed by Raman Spectroscopy will provide numerical scores that will be correlated with motor parameters obtained after treatment to identify prognostic biomarkers of rehabilitation outcome).

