Indeed, since the effect of rehabilitation may be different across motor subtypes (27) and disease severity (8), treatment personalization holds promise in PD rehabilitation. However, a timely optimization of personalized rehabilitation treatment for PD patients is nowadays at least in part limited by the lack of measurable biomarkers indicative of neuroplasticity phenomena and predictive of the response to the rehabilitation treatment. In this regard, Neurofilament Light Chain (NfL) has been recognized as a non-specific marker indicative of axonal damage in different neurological diseases (28–30), whereas it is not fully understood whether and how its concentration changes after rehabilitation treatment. In late phase after stroke the adaptive synaptic plasticity is supposed to be the main mechanism of NfL release, suggesting that this biomarker could also be useful to track the positive effects following rehabilitation (29). Recent literature suggests that neuroplasticity phenomena can be investigated with other innovative approaches, spanning from quantification of single molecules with highly sensitive technologies to more complex biomarkers like miRNome profile and circulating Extracellular Vesicles (cEVs) characterization. The study of the cellular processes taking place in the central nervous system in patients with PD before, during, and after rehabilitation might provide useful tools to correlate the severity of the damage and the peculiarities of the patient with the effectiveness of treatment. cEVs are natural nanoparticles defined as membrane-bound nanovesicles, released by body cells under physiological and pathological conditions as vehicles for bioactive molecules useful for intercellular communication. It has recently been demonstrated that biological fluids are rich in such vesicles, in particular vesicles originating from all the organs of our body, including the central nervous system, circulate in the blood (31). cEVs may change in concentration, dimension and biochemical content as a consequence of pathological processes and possibly after rehabilitation. In patients with PD, vesicles appear to play a role in the transport of molecules involved in the pathogenetic mechanisms of the disease itself, such as for example in the transport of the alpha-synuclein protein at the cerebral and peripheral level (32). The presence of cEVs involved in the pathogenesis and evolution of the disease and carriers of potential diagnostic markers has been demonstrated in peripheral blood (33). However, the size, heterogeneity, and large number of molecules present within and on cEVs have limited their use for diagnostic purposes. Raman spectroscopy is proposed as a useful method for the rapid and exhaustive biochemical characterization of circulating exosomes without the use of staining and labeling procedures. It has already been demonstrated how the Raman signature of cEVs can be correlated with some clinical scales commonly used for PD patient profiling, suggesting their potential use for patient stratification (34).

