
In summary, the evidence of the potential superiority of TT + AVR versus TT to improve gait in PD is still preliminary, and few studies include both clinical and instrumental gait measures, as it is instead recommended (3); further, an optimal TT(+AVR) protocol, customized to patients’ performances has not been established; finally, potential biomarkers of neuroplasticity and prognostic biomarkers are still under study.

Taking into account these considerations, the primary objective of this study is to compare the effects on gait performances of an integrated rehabilitation intervention before and after intensive rehabilitation with TT endowed of AVR, versus TT alone in patients with PD in II-III Hoehn and Yahr stage (35) with gait disturbances. The secondary objectives are to assess the effects of the interventions on balance performances, kinematic gait parameters and other motor and non motor symptoms immediately after treatment and at a 3-months follow up, and to assess the patient’s satisfaction and adherence to the treatment. The exploratory objective is to investigate potential serum biomarkers of neuroplasticity and prognosis.

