#### Data analysis

2.7.2

Statistical analysis will be conducted using the software SPSS v28 (Armonk, NY: IBM Corp). The distribution will be assessed using the Kolmogorov–Smirnov test for all clinical and instrumental continuous data, assuming the presence of normal distribution when *p* > 0.05. Data will then be summarized as mean and standard deviation, median and interquartile range, or absolute and percentage frequency, as appropriate.

The experimental and the control groups will be compared at baseline to explore significant differences in demographic, clinical, and instrumental variables. Parametric or non-parametric tests will be used for continuous variables, according to data distribution. The chi-square test will be used to compare distributions of binary/categorical variables.

Both within and between-group analyses will be conducted to assess at each time point the effects of the treatments delivered, for primary and secondary outcome measures. Specifically, a two-way repeated measures ANOVA will be used with a within-factor (time of assessment) and a between-factor (group).

Regarding biological data, the acquired Raman spectra will be analyzed by multivariate Principal Component Analysis – Linear Discriminant Analysis (PCA-LDA) classification. PCA will reduce the number of variables into principal components, which will be used to build the LDA model. The model will be built to discriminate clinical improvement detected as quantifiable change on clinical scales, defined based on the minimum clinically important difference, when available from the literature. The sensitivity, specificity, and accuracy of the predicting model based on spectra data will be assessed. In addition, correlation analysis will be conducted to evaluate the association between spectral data and change on clinical scales recorded between the treatment’s beginning and end. Statistical analysis of the Raman data will be performed using Origin2023b (OriginLab Corporation, Northampton, MA, USA) (34).

Univariate analysis models will be used to select the best prognostic markers of clinical improvement to be included in a multivariate model.

For all analyses, statistical significance will be set at *p* < 0.05.

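### Correlating the T0 Raman score with post-treatment motor values, without the T0 motor value, cannot separate prediction of recovery from current severity

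*Protocol article*

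**What the plan says.** Section 2.6 (Outcome measures) fixes marker, endpoint, method and conclusion in one sentence: Raman scores from T0 "will provide numerical scores that will be correlated with motor parameters obtained after treatment to identify prognostic biomarkers of rehabilitation outcome". The endpoint is the level after treatment, and no T0 motor value enters.

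Section 2.7.2 (Data analysis) adds three further steps:

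- A second correlation, on change: "correlation analysis will be conducted to evaluate the association between spectral data and change on clinical scales recorded between the treatment’s beginning and end".
- A PCA-LDA classifier: "The model will be built to discriminate clinical improvement detected as quantifiable change on clinical scales", with improvement defined by the minimum clinically important difference where the literature gives one.
- A model-building step: "Univariate analysis models will be used to select the best prognostic markers of clinical improvement to be included in a multivariate model". Its covariates are not listed.

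The Introduction says that "the Raman signature of cEVs can be correlated with some clinical scales commonly used for PD patient profiling", without giving the strength of the correlation or naming the gait measures used here. It also sets the status of this work: "The exploratory objective is to investigate potential serum biomarkers of neuroplasticity and prognosis". Section 2.4 confirms that baseline motor values exist: "The same assessment protocol will be performed at each time point (T0, T1, T2) with some exceptions". Section 2.7.2 applies the 0.05 significance level to all analyses.

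**The concern.** Parkinson's disease is chronic, training lasts 8 weeks and drug therapy is held stable until T1. Patients who walk poorly at T0 will mostly be the ones who walk poorly at T1. A blood score that tracks present impairment will then correlate with the T1 value even if it says nothing about who gains from training. The link from marker to severity is not speculative, because the article itself cites it.

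The Introduction wants markers that foretell response to rehabilitation, and the abstract wants them to help customise treatment. A marker that restates the baseline gait score serves neither purpose. Internal validation would not expose the problem: the correlation with T1 is real and would replicate, but it is not about recovery.

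**Working it through.** **Sample available.** The article gives no figure for the prognostic analysis, so n comes from the sample size in section 2.2. Pooled SD = √((1.1² + 0.5²)/2) = 0.854, and d = (11.7 − 10.7)/0.854 = 1.17. A two-sided two-sample t-test at 0.05 with 95% power needs 20 per arm, as stated. I use n = 40, the number left after the planned dropout allowance from 48.

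**Assumptions, not in the documents.** ρ is the correlation of the marker with the T0 motor value, 0.3 to 0.6. r is the T0-T1 correlation of the motor measure, 0.6 to 0.8. SDs are equal at T0 and T1, and tests are two-sided at 0.05. In every case the marker carries severity and nothing else.

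**Structure A: the marker tracks the observed T0 score.** Expected correlations:

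- with T1: ρr
- with change: −ρ√((1 − r)/2)
- with T1 given T0: 0

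**Structure B: the marker tracks stable underlying severity, and T0 and T1 are two noisy readings of it.** Expected correlations:

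- with T1: ρ
- with change: 0
- with T1 given T0: ρ(1 − r)/√((1 − ρ²)(1 − r²))

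Percentage of trials in which the pure severity marker is significant (simulation, 20,000 runs per cell, n = 40):

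| ρ, r | A: T1 level | A: change | A: T0-adjusted | B: T1 level | B: change | B: T0-adjusted |
|---|---|---|---|---|---|---|
| 0.3, 0.6 | 20 | 13 | 5 | 48 | 5 | 16 |
| 0.3, 0.8 | 32 | 9 | 5 | 48 | 5 | 9 |
| 0.5, 0.6 | 48 | 29 | 5 | 92 | 5 | 43 |
| 0.5, 0.8 | 74 | 17 | 5 | 92 | 5 | 22 |
| 0.6, 0.6 | 65 | 39 | 5 | 99 | 5 | 67 |
| 0.6, 0.8 | 89 | 22 | 5 | 99 | 5 | 34 |

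**Hand check of the extremes by Fisher's z.** Multiply atanh of the expected correlation by √37 = 6.083 (simple) or √36 = 6 (one covariate), and compare with 1.96.

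- A, T1 level, 0.3 × 0.6 = 0.18: 0.182 × 6.083 = 1.11, giving about 20%.
- A, T1 level, 0.6 × 0.8 = 0.48: 0.523 × 6.083 = 3.18, giving about 89%.
- B, T1 level, 0.3: 0.310 × 6.083 = 1.88, giving about 47%. At 0.6: 0.693 × 6.083 = 4.22, giving about 99%.
- B, T0-adjusted, ρ = r = 0.6: 0.6 × 0.4/(0.8 × 0.8) = 0.375; 0.394 × 6 = 2.37, giving about 66%.

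**Reference case.** With ρ = 0, all three analyses stay near 5%.

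**Reading.** In every cell the unadjusted T1 correlation has the highest false-positive rate. T0 adjustment always lowers it, fully under A and in part under B. Raw change is sound under B and inflated under A.

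**The case against.** The strongest reply has four parts.

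*Change is already analysed.* Section 2.7.2 correlates spectra with change, and under structure B that test holds 5% while T0 adjustment does not. Structure B is plausible: a serum marker more naturally follows underlying severity than one observed score, and the Discussion itself reports that the POMA has low sensitivity and is open to tester bias. This stands. A reader might infer that the change analysis is an error to be removed, or that it must contradict the level analysis in sign. The documents do not support either reading, because the opposite sign appears only under structure A with the assumed variances.

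*The multivariate model may contain T0.* Its covariates are neither stated nor ruled out, and a condensed article may leave that list to a fuller document. This also stands, and the missing list is not a fault. It does not repair the rule in section 2.6, which says on its own terms how prognostic markers are to be identified.

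*The size is unknown.* The article gives no value for either correlation, and restricting enrolment to Hoehn and Yahr II-III may weaken the link with severity. A reader might infer that a false claim will be made. The documents support only that it can be.

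*The stakes are low.* The objective is exploratory and T0 data are collected, so adjustment remains possible later. True, but the published rule draws the prognostic conclusion without it.

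**Conclusion.** The point holds for the test in section 2.6. As written, it cannot tell a marker of recovery from a marker of present impairment, and the article's own evidence makes the second plausible. A pure severity marker would be declared prognostic in about 20% to 89% of trials under structure A and about 48% to 99% under structure B. The rate falls to about 5% if the marker is unrelated to severity. These ranges rest on n = 40, equal SDs and the assumed correlations.

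A reader might also infer that T0 adjustment settles the matter. It does so only under structure A. Under structure B the adjusted rate is still about 9% to 67%, because an error-prone T0 score removes only part of the severity effect. Adjustment is nevertheless better than the unadjusted T1 correlation in every cell where the marker carries severity.

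The consequence is confined to an exploratory objective. The primary comparison and the sample size are untouched.

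**What to change.** 1. In section 2.6, replace the unadjusted correlation with post-treatment values by a regression of the T1 motor measure on the T0 Raman score, with the T0 value of the same measure and treatment arm as covariates.
2. Keep the change analysis of section 2.7.2 beside it. Call a marker prognostic only if it adds information beyond T0 and arm and the two analyses agree in direction. The direction check is a partial filter: under structure B the change correlation is centred on zero, so its sign will sometimes agree by chance.
3. Report the PCA-LDA accuracy against a model that uses only the T0 clinical score and arm.
4. State that T0 adjustment reduces confounding by severity but does not fully remove it when the T0 scale is measured with error.

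The cost is wording in sections 2.6 and 2.7.2, because all the variables are already collected. The downside is fewer nominally positive exploratory associations.
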